### Outcome

Primary outcomes will include changes in cognitive function, and changes in imaging biomarkers, before and after taking KGT or placebo granules. For assessing cognitive function, the SNSB will be conducted and changes in SNSB results will be analyzed. For measuring the imaging biomarkers, brain MRI scans will be taken to assess the levels of brain metabolites, neurotransmitters, and cerebral blood flow (CBF).

Secondary outcomes will include the safety of KGT granules, and changes in blood-based biomarkers including proteins (amyloid β (Aβ) and tau) and cholesterols, and a comparison of MRI changes between the two groups using age and genotype as covariates. For safety assessments, blood chemistry tests for AST/ALT, glucose, blood urea nitrogen (BUN), Cr, Na, K, Cl, lactate dehydrogenase (LDH), creatine phosphokinase (CPK), and an electrocardiogram (ECG) will be conducted. Blood biomarkers including Aβ protein, tau protein, high-mobility group box (HMGB), small EDRK-rich factor (SERF) 1A, and cholesterol derivatives will also be measured. *APOE* genotype testing will be performed. Detailed explanations are shown below.

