### Assessments

#### K-MMSE and SNSB

The K-MMSE will be performed at the screening visit and after 12 weeks of medication, to screen for MCI and assess the cognitive status of participants. This is a simple screening test for the longitudinal assessment of general cognition [10].

The full version of the SNSB-II will be measured at baseline and after 24 weeks of medication, to evaluate the effect of *Kami Guibi-tang* on cognitive function. The change in the mean of the SNSB scores, including the SNSB for dementia (SNSB-D) scores, will be compared between the KGT and placebo groups as a primary outcome.

The SNSB is one of the standardized neuropsychological test batteries, widely used in South Korea, for assessing general cognitive abilities. The test is composed of multiple subtests, which evaluate five cognitive aspects: attention, memory, language, visuospatial function, and executive function. Other related tests are included, such as the K-MMSE, Clinical Dementia Rating (CDR), Barthel–Activities of Daily Living (BADL), and Geriatric Depression Scale (GDS). The estimated completion time of the whole battery is 1.5–2 h [11].

A modified version of the original SNSB for dementia (SNSB-D) will be used to provide a general cognitive functioning (GCF) score, drawn from the sum of five domains. The maximum total score is 300 points consisting of 17/300 (6%) for attention, 27/300 (9%) for language and related function, 36/300 (12%) for visuospatial function, 150/300 (50%) for memory, and 70/300 (23%) for frontal/executive function [12]. The contents of the SNSB-D are shown in Table 2.

**Table 2 Tab2:** Contents of the Seoul Neuropsychological Battery for Dementia (SNSB-D)

Domains (total score)	Subtests	Maximum points
Attention (17)	Digit span forward	9
	Digit span backward	8
Language and related function (27)	K-BNT	15
	Calculation	12
Visuospatial function (36)	RCFT copy	36
Memory (150)	Orientation	6
	SVLT free/delayed recall	48
	SVLT recognition	12
	RCFT free/delayed recall	72
	RCFT recognition	12
Frontal/executive function (70)	Motor impersistence	3
	Contrasting program	3
	Go-no-go test	3
	Fist-edge-palm	3
	Luria loop	3
	Categoric word generation	20
	Phonemic word generation	15
	Stroop test-color reading	20
GCF score		300

*K-BNT* Korean short version of the Boston Naming Test, *RCFT* Rey Complex Figure Test, *SVLT* Seoul Verbal Learning Test, *GCF* global cognitive function

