#### MRI

Participants will undergo brain MRI at baseline and after 24 weeks of medication, to measure changes in brain metabolite and neurotransmitter levels, cerebral blood flow, tissue volume, and to evaluate brain abnormalities.

Proton magnetic resonance spectroscopy (^1^H-MRS) will be used to measure brain metabolite and neurotransmitter levels. Single-voxel Point-RESolved Spectroscopy (PRESS) MRS will be performed at the precuneus and posterior cingulate area of the brain, with a voxel size of 30 mm × 30 mm × 30 mm, to detect *N*-acetylaspartate (NAA) and glutamate-glutamine complex (Glx, with both Glu and Gln). *N*-acetylaspartate and Glx will be quantified using LCModel software. MEshcher-GArwood (MEGA) PRESS MRS will be performed to detect gamma-aminobutyric acid (GABA) in the same area as the PRESS MRS. The amount of GABA will be quantified using GANNET software. Pseudo-continuous arterial spin-labeling (pCASL) MRI will be performed to measure cerebral blood flow (CBF) in the brain. Voxel-based CBF will be mapped using local software. A three-dimensional T1-weighted image will be acquired using the magnetization-prepared rapid gradient-echo (MPRAGE) sequence, to quantify the gray and white matter tissue volume in the brain. T2-weighted turbo-spin echo (TSE), and fluid attenuation inversion recovery (FLAIR) sequences, will be used to evaluate brain abnormalities in participants. Changes in CBF and mean levels of NAA/Cr, Glx/Cr, and GABA/Cr, will be compared between KGT and placebo groups, as a primary outcome.

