### Statistics

#### Sample size calculation

This clinical trial is a pilot study to examine the feasibility of a full randomized clinical trial of KGT, and to determine the sample magnitude required for large-scale studies. To our knowledge, no prior study has investigated the effect of KGT on MCI. There are no previous data indicating the sample size needed to yield statistically significant results for determining the effect of KGT by the SNSB scores. For pilot trials, the sample size of 10–20 participants per group was suggested by Kieser and Wassmer. [13]. Browne recommended using at least 30 subjects to estimate parameters [14]. Our target sample size is 30, so 38 individuals will be recruited to allow for a 20% dropout rate.

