#### Data analyses

The investigators, along with an independent professional statistician, will perform the data analyses. All statistical analyses will be performed using SPSS for Windows. The effectiveness test will be performed using the intention-to-treat (ITT) principle and the per-protocol (PP) principle. Missing data will be adjusted with the last-observation-carried-forward (LOCF) imputation method. The safety test will be analyzed using the ITT principle, without adjustment. We will not perform interim analysis.

The student’s *t* test will be used for parametric variable comparisons between the two groups, and the paired *t* test will be used for intra-group comparisons. The Mann-Whitney *U* test will be used for non-parametric variable comparisons between the two groups, and the Wilcoxon signed-rank test will be used for intra-group comparisons.

The paired *t* test will be used to compare changes in MRI measurements, blood proteins, and cholesterol levels, before and after treatment. Correlation analysis will be used to estimate the relationship between the changes in MRI measures and changes in blood test results. Linear regression analysis will be used to compare changes in MRI measures, between the study group and the placebo group, using age and *APOE* genotype as covariates. Statistical significance will be set at *P* < 0.05, and all tests will be two-tailed.

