Proton MRS is a sensitive method for estimating brain metabolite and neurotransmitter concentrations [22], including NAA, myo-Inositol (mI), choline (Cho), Glx, and GABA, frequently measured as ratios to creatine [23]. A decrease in concentrations of NAA, a neuronal metabolite, and Glx, a component of the excitatory neurotransmitter system in the brain, is indicative of neuronal dysfunction in AD [24]. Detecting changes in neuronal markers may be suitable for assessing treatment responses.

Arterial spin-labeling perfusion MRI (ASL MRI) is used to quantify regional cerebral blood flow (rCBF) [25]. Alzheimer’s disease patients show regional hypoperfusion that reflects patterns of reduced brain functional activity, using this technique [26]. Studies have suggested that ASL MRI is appropriate for examining neural response to pharmacological agents [27]. Prior studies that measured rCBF used Single Photon Emission Computed Tomography (SPECT). However, ASL MRI is advantageous because there is no exposure to ionizing radiation or the need for intravenously administered contrast agents, and there is higher accessibility, lower cost, and higher spatial resolution [26].

As secondary outcomes, we will observe changes in blood-based biomarkers levels, including Aβ protein, tau protein, HMGB, SERF 1A, and cholesterol derivatives, which are proposed to be associated with AD pathology [28]. Aβ protein and tau proteins are the main feature of AD neuropathology, and are closely associated with neuronal loss. High plasma Aβ levels are a risk factor for AD [29]. High total cholesterol levels accelerate the production of Aβ protein in AD, and are related to increased cognitive impairment in humans [30]. The strongest genetic risk factor for AD, *APOE* genotype, will also be determined by plasma *APOE* proteins [31]. This genetic marker will provide information for distinguishing which patients are most likely to benefit from KGT administration.

This pilot study will be the first rigorous clinical analysis of KGT for the treatment of aMCI, and should provide evidence for the effectiveness and safety and of KGT. Our extensive assessment, using various biomarkers, should reveal the mechanisms underlying the effect of KGT on disease progression. The findings will support a large-scale confirmatory clinical trial to gather evidence for KGT use in MCI patients.

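### At least five unranked primary outcomes, each tested at two-sided P<0.05, do not fit a trial sized for feasibility that also promises evidence of effectiveness

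*Protocol article*

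**What the plan says.** The Outcome section makes two families primary, cognition and imaging, in open-ended terms: "Primary outcomes will include changes in cognitive function, and changes in imaging biomarkers, before and after taking KGT or placebo granules".

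For cognition, the K-MMSE and SNSB section takes as primary "The change in the mean of the SNSB scores, including the SNSB for dementia (SNSB-D) scores", in the plural. The same section says that the SNSB-D "will be used to provide a general cognitive functioning (GCF) score, drawn from the sum of five domains", with a maximum of 300 points, but it does not choose that total as the deciding measure.

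For imaging, the MRI section lists CBF, NAA/Cr, Glx/Cr and GABA/Cr, which "will be compared between KGT and placebo groups, as a primary outcome".

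Data analyses sets a single two-sided 0.05 level for all tests. Effectiveness is analysed under both ITT and PP, and neither is named as leading.

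On purpose, Sample size calculation says: "This clinical trial is a pilot study to examine the feasibility of a full randomized clinical trial of KGT". The Discussion says that the study "should provide evidence for the effectiveness and safety and of KGT", and the Background gives determining effectiveness as an aim. The Abstract and the opening of the Discussion speak only of exploring, and the Discussion also points to a later confirmatory trial and lists the small sample as a limitation.

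**The concern.** If several outcomes share primary status and any of them can be declared significant at 0.05, the 5% error rate applies to each test and not to the trial. A reader who takes one significant primary as support for the treatment is using a rule with a much higher error rate than the stated level suggests.

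That would matter less if the results were presented only as estimates. Here the primary label, the significance threshold and the effectiveness wording stand together, in a trial whose size was not derived from any effect, standard deviation or power. A chance finding on one MRI ratio could become the stated rationale for the larger trial. A null finding could equally be over-read, because only large differences can reach significance at this size.

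**Working it through.** **Inputs from the article**
- Two-sided level 0.05 for all tests (Data analyses).
- Allocation 1:1 (Randomization, allocation, blinding).
- Target of 30, with 38 recruited to allow for 20% dropout (Sample size calculation).
- Imaging primaries: CBF, NAA/Cr, Glx/Cr, GABA/Cr = 4 (MRI). CBF is counted once, which is a lower bound because it is mapped by voxel.
- Cognitive primaries: at least the GCF total = 1; with the five SNSB-D domains = 6 (K-MMSE and SNSB, Table 2).

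**Assumed, because the article gives no values:** the correlations between outcomes, and a true effect of 0.5 SD for the power illustration.

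**1. The plan's own figure.** 30 / (1 − 0.20) = 37.5, rounded up to 38. This reproduces. The 30 itself comes from pilot-size rules of thumb, so there is no power statement to reproduce. It gives about 15 completers per arm, or 19 per arm if all 38 are analysed under ITT.

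**2. Number of primaries.** Minimum: 1 + 4 = 5. With the domains: 1 + 5 + 4 = 10.

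**3. Chance of at least one significant primary under no effect.** If independent, this is 1 − 0.95^k:
- k = 5: 1 − 0.774 = 0.226
- k = 10: 1 − 0.599 = 0.401

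With equal correlation between outcomes (simulated two-sample t tests, 15 per arm; 19 per arm agrees to within half a percentage point):

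| Assumed correlation | 5 outcomes | 10 outcomes |
|---|---|---|
| 0 | 23% | 40% |
| 0.5 | 19% | 29% |
| 0.8 | 13% | 18% |

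These figures cover one analysis set only. Testing in both ITT and PP would add to them.

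**4. Smallest difference that can be significant.** In SD units this is t(0.975, 2n − 2) × √(2/n):
- n = 15 per arm: 2.048 × √(2/15) = 0.75 SD
- n = 19 per arm: 2.028 × √(2/19) = 0.66 SD

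**5. Power for one outcome at an assumed 0.5 SD effect** (two-sample t test, level 0.05): 26% with 15 per arm and 32% with 19 per arm.

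**6. Could the five stay co-equal with an adjustment?** Bonferroni gives 0.05/5 = 0.01 per test. At 15 per arm and 0.5 SD, power falls from 26% to 10%. Ranking the outcomes therefore suits this design better than splitting the level.

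**The case against.** The strongest reply is that this is a pilot, that pilots properly measure many things, and that the article often says so: it speaks of exploring, defers confirmation to a later trial and admits the small sample. All of this stands, and it makes the effectiveness wording an inconsistency within the article and not its settled message. It does not remove the wording in the Background and Discussion, or the primary label and threshold attached to every measure.

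A second reply is that a multiplicity rule, or the choice of SNSB score, may sit in a full protocol or analysis plan that is not shown. That is possible, and the lack of a rule here would be no finding by itself. The point rests on what the article does fix: several unranked primaries, one threshold for all, and an effectiveness aim.

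A reader might infer three stronger things that the article does not support:
- **That a false-positive primary is likely.** Every figure for 5 to 10 outcomes is below one half. Independence is the upper end, since the GCF is the sum of its own domains.
- **That there are definitely ten primaries.** The article uses the plural for the scores but does not say that each domain is a separate primary test. Five is the secure count.
- **That a significant, and so exaggerated, effect will be used to plan the next trial.** The article says only that the pilot will inform the later sample size. It does not say that an observed effect will be used for this.

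**Conclusion.** The point holds as an internal mismatch that is cheap to repair. At least five unranked primaries at an unadjusted 0.05 put the chance of one or more false-positive primaries at about 13–23% for five outcomes and 18–40% for ten, or roughly three to eight times the nominal 5%. The range runs from an assumed correlation of 0.8 to independence. The counts and the level come from the article; the correlations do not.

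Precision is too low for an effectiveness claim in either analysis set. Only observed differences of at least 0.66 SD (19 per arm) to 0.75 SD (15 per arm) can be significant, and under the assumed 0.5 SD effect a single test would miss it about two times in three or more. The design can support estimation and feasibility. It cannot support a conclusion on effectiveness drawn from whichever primary is significant.

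**What to change.** By dated amendment to the protocol and registry entry, before unblinding:

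1. Name one primary outcome: the between-group difference in SNSB-D GCF score at week 24, adjusted for baseline GCF, in the ITT set. Give the PP analysis as a sensitivity analysis. Adjusting for baseline keeps the information now carried by the change score and protects against chance imbalance in small arms.
2. Make the domain scores, NAA/Cr, Glx/Cr, GABA/Cr and CBF secondary or exploratory, reported as estimates with 95% confidence intervals. The covariate-adjusted MRI comparison is already listed as secondary.
3. Restate the aim in the Background and the expected contribution in the Discussion as estimation and feasibility, in line with Sample size calculation.

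No measurement is added or dropped. The costs are that the MRI results carry an exploratory label, the claim becomes more modest, and a late change of primary outcome has to be disclosed: Trial status reports 33 participants already enrolled. No interim analysis is planned, so the change can still be made without knowledge of results by arm.

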### Assessments

#### K-MMSE and SNSB

The K-MMSE will be performed at the screening visit and after 12 weeks of medication, to screen for MCI and assess the cognitive status of participants. This is a simple screening test for the longitudinal assessment of general cognition [10].

The full version of the SNSB-II will be measured at baseline and after 24 weeks of medication, to evaluate the effect of *Kami Guibi-tang* on cognitive function. The change in the mean of the SNSB scores, including the SNSB for dementia (SNSB-D) scores, will be compared between the KGT and placebo groups as a primary outcome.

The SNSB is one of the standardized neuropsychological test batteries, widely used in South Korea, for assessing general cognitive abilities. The test is composed of multiple subtests, which evaluate five cognitive aspects: attention, memory, language, visuospatial function, and executive function. Other related tests are included, such as the K-MMSE, Clinical Dementia Rating (CDR), Barthel–Activities of Daily Living (BADL), and Geriatric Depression Scale (GDS). The estimated completion time of the whole battery is 1.5–2 h [11].

A modified version of the original SNSB for dementia (SNSB-D) will be used to provide a general cognitive functioning (GCF) score, drawn from the sum of five domains. The maximum total score is 300 points consisting of 17/300 (6%) for attention, 27/300 (9%) for language and related function, 36/300 (12%) for visuospatial function, 150/300 (50%) for memory, and 70/300 (23%) for frontal/executive function [12]. The contents of the SNSB-D are shown in Table 2.

**Table 2 Tab2:** Contents of the Seoul Neuropsychological Battery for Dementia (SNSB-D)

Domains (total score)	Subtests	Maximum points
Attention (17)	Digit span forward	9
	Digit span backward	8
Language and related function (27)	K-BNT	15
	Calculation	12
Visuospatial function (36)	RCFT copy	36
Memory (150)	Orientation	6
	SVLT free/delayed recall	48
	SVLT recognition	12
	RCFT free/delayed recall	72
	RCFT recognition	12
Frontal/executive function (70)	Motor impersistence	3
	Contrasting program	3
	Go-no-go test	3
	Fist-edge-palm	3
	Luria loop	3
	Categoric word generation	20
	Phonemic word generation	15
	Stroop test-color reading	20
GCF score		300

*K-BNT* Korean short version of the Boston Naming Test, *RCFT* Rey Complex Figure Test, *SVLT* Seoul Verbal Learning Test, *GCF* global cognitive function

#### MRI

Participants will undergo brain MRI at baseline and after 24 weeks of medication, to measure changes in brain metabolite and neurotransmitter levels, cerebral blood flow, tissue volume, and to evaluate brain abnormalities.

Proton magnetic resonance spectroscopy (^1^H-MRS) will be used to measure brain metabolite and neurotransmitter levels. Single-voxel Point-RESolved Spectroscopy (PRESS) MRS will be performed at the precuneus and posterior cingulate area of the brain, with a voxel size of 30 mm × 30 mm × 30 mm, to detect *N*-acetylaspartate (NAA) and glutamate-glutamine complex (Glx, with both Glu and Gln). *N*-acetylaspartate and Glx will be quantified using LCModel software. MEshcher-GArwood (MEGA) PRESS MRS will be performed to detect gamma-aminobutyric acid (GABA) in the same area as the PRESS MRS. The amount of GABA will be quantified using GANNET software. Pseudo-continuous arterial spin-labeling (pCASL) MRI will be performed to measure cerebral blood flow (CBF) in the brain. Voxel-based CBF will be mapped using local software. A three-dimensional T1-weighted image will be acquired using the magnetization-prepared rapid gradient-echo (MPRAGE) sequence, to quantify the gray and white matter tissue volume in the brain. T2-weighted turbo-spin echo (TSE), and fluid attenuation inversion recovery (FLAIR) sequences, will be used to evaluate brain abnormalities in participants. Changes in CBF and mean levels of NAA/Cr, Glx/Cr, and GABA/Cr, will be compared between KGT and placebo groups, as a primary outcome.

#### Blood testing

Amyloid β protein, tau protein, HMGB, SERF 1A, and cholesterol derivatives will be measured in the blood at baseline and after 24 weeks of medication to observe changes in serum proteins and cholesterol associated with AD pathology. Changes in mean values of blood biomarker levels will be compared between the KGT and placebo groups.

#### Genotyping

Apolipoprotein E (*APOE*) epsilon genotyping (e23, e33, e34, e44) will be performed using blood samples at baseline, to determine if the effect of KGT is influenced by *APOE* genotype. The changes in mean values of NAA/Cr, Glx/Cr, GABA/Cr, and CBF before and after the intervention will be compared between carriers and non-carriers of the *APOE* epsilon 4 allele.

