### Randomization, allocation, blinding

A researcher uninvolved in the assessment will generate a random sequence using SPSS ver. 18. We will randomly allocate participants to either the treatment or the control group, in a 1:1 ratio using the block randomization method, with a block size of 4. The participants, assessor, clinical trial pharmacist, and researchers will be blinded to the allocations throughout the course of the study. Cases will be unblinded only if serious adverse events (SAE) occur.

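### The APOE analysis stated for effect modification compares e4 carriers with non-carriers, which mixes prognosis with modification of the KGT effect and cannot separate them

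*Protocol article*

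**What the plan says.** The Genotyping section gives the purpose of APOE typing: "to determine if the effect of KGT is influenced by" genotype. Its next sentence gives the analysis. Mean changes in NAA/Cr, Glx/Cr, GABA/Cr and "CBF before and after the intervention will be compared between carriers and non-carriers of the" epsilon 4 allele. That sentence mentions neither KGT nor placebo. The MRI and Blood testing sections just before it both name the comparison as one between the KGT and placebo groups.

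Genotype appears in one other analysis. The Outcome section lists, as secondary, "a comparison of MRI changes between the two groups using age and genotype as covariates". The Data analyses section implements it: "Linear regression analysis will be used to compare changes in MRI measures, between the study group and the placebo group". That model adjusts for age and for APOE genotype. No arm-by-genotype term is stated, and no KGT-placebo contrast within genotype groups.

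The Discussion then draws the inference: "This genetic marker will provide information for distinguishing which patients are most likely to benefit from KGT administration".

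**The concern.** Whether a treatment effect depends on genotype is a question about a difference of differences: KGT minus placebo in carriers, less KGT minus placebo in non-carriers. A comparison of carriers with non-carriers does not estimate that. If carriers change differently over 24 weeks whatever they take, the comparison shows a difference even when KGT acts equally in both groups, or not at all. Prognosis running against a real interaction can also hide it.

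The covariate regression does not fill the gap. Genotype as a main effect adjusts the arm comparison but fits one KGT effect common to carriers and non-carriers.

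At stake is a statement about which patients benefit, carried from this pilot into the planning of the larger trial that it is meant to support.

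**Working it through.** **Inputs from the article.** The target is 30 evaluable participants (Sample size calculation: "Our target sample size is 30, so 38 individuals will be recruited to allow for a 20% dropout rate"). This reproduces: 30 / (1 − 0.20) = 37.5, rounded up to 38. Allocation is "in a 1:1 ratio using the block randomization method, with a block size of 4", so about 15 per arm among 30. Tests are two-sided at 0.05. The article gives no figure for the APOE analysis.

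**Assumptions, since the article gives none.** Change scores have unit SD. The main case is 40% carriers (12 v 18 overall, 6 v 9 per arm), with other shares shown. The prognostic gap ranges from 0 to 0.8 SD.

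**What each contrast estimates.** Write mean change as a + p·C + t·T + i·T·C, where C = 1 for carriers and T = 1 for KGT. Here p is prognosis, t the KGT effect in non-carriers and i the interaction.

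- Arms pooled, half of each genotype group on KGT: (a + p + t/2 + i/2) − (a + t/2) = p + i/2.
- KGT arm only: (a + p + t + i) − (a + t) = p + i.
- KGT minus placebo in carriers, less the same in non-carriers: (t + i) − t = i.

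Only the third isolates i.

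**Significant results with no effect modification (i = 0).** Two-sample t test, noncentrality p × √(n1·n2/(n1+n2)). The root is 2.683 for 12 v 18 and 1.897 for 6 v 9.

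| Prognostic gap (SD) | Pooled, 12 v 18 | KGT arm only, 6 v 9 |
|---|---|---|
| 0 | 5% | 5% |
| 0.2 | 8% | 6% |
| 0.4 | 18% | 11% |
| 0.6 | 34% | 18% |
| 0.8 | 54% | 29% |

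Carrier share matters. At 20% carriers (6 v 24) the pooled figure at 0.8 SD is 40%.

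Simulation (20,000 trials, 15 per arm, 4, 6 or 7 carriers per arm) agrees. With a 0.8 SD gap and an equal KGT effect of 0.5 SD in both groups, the pooled test rejects in 44-53% of trials, the KGT-arm test in 25-30%, and the interaction test in about 5%.

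**A real interaction can vanish.** With i = 1 SD and p = −0.5 SD, p + i/2 = −0.5 + 0.5 = 0. In simulation the pooled test rejects in about 4% of trials and the interaction test in 22-26%.

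**Precision of the right estimate.** With carriers split evenly between arms, SE(i) = √(4 / (30·f·(1 − f))) for carrier share f. At f = 0.4 this is √(4/7.2) = 0.745 SD. The main-effect SE is √(2/15) = 0.365 SD, about half. With t(0.975, 26) = 2.056, the 95% CI half-width is 2.056 × 0.745 = 1.53 SD. It is 1.50 at f = 0.5 and 1.64 at f = 0.3. A 4/8 split of the 12 carriers gives SE √(1/4 + 1/8 + 1/11 + 1/7) = 0.780 and ±1.60.

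**The case against.** **The contrast is not pure prognosis.** A reader might infer that the carrier comparison measures prognosis and nothing else. It does not: pooled, it carries half of any interaction. The defect is that the two parts cannot be told apart.

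**Pooling is one reading.** The Genotyping sentence does not say whether arms are pooled or taken separately, so the pooled percentages apply to one reading only. Within the KGT arm the figures are lower, but prognosis is still mixed in. Carrier comparisons in both arms would come closer to the aim, but they would still have to be subtracted from each other, and the article states no such step.

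**The error rates rest on an assumed gap.** The Discussion calls APOE the strongest genetic risk factor for AD, which makes a prognostic difference plausible. It gives no rate of change in spectroscopy or blood-flow measures over 24 weeks. If there is no gap, the rejection rate is the nominal 5%. This limits the size of the problem but does not remove the mismatch between aim and contrast.

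**An article condenses.** A reader might infer that no analysis of the interaction is planned anywhere. The full protocol and any SAP are not shown, so one can say only that this article states none. But the article does fix a contrast for the stated aim, and a later document would have to replace it, not merely add detail.

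**The genotype list.** The listed genotypes omit e24, and a reader might infer misclassification. The groups are defined by carrying the epsilon 4 allele, so e24 would count as a carrier. Nothing follows from the list.

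**The stakes are modest.** The carrier comparison is not listed as a primary or secondary outcome, and this is an exploratory pilot of 30. Even the right test has only about 22-26% power for a 1 SD interaction. That argues for an exploratory label, not for keeping a contrast that targets a different quantity at any sample size.

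**Conclusion.** The concern holds as a mismatch between question and analysis. The article asks whether genotype modifies the KGT effect, states a carrier comparison that confounds modification with prognosis, and otherwise uses genotype only for adjustment. This conclusion follows from the algebra on either reading and needs no assumed figure.

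The size of the error does depend on assumptions. With 12 v 18 and no modification, the chance of a significant pooled result runs from 5% with no prognostic gap to 54% with a gap of 0.8 SD. Restricted to the KGT arm, it reaches 29%. The documents do not support saying that a false signal is certain, or that the comparison carries no information on modification. The Discussion claim goes further than any stated analysis could support, and further than 30 participants could support even with the right model. It needs softening, not removal.

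**What to change.** In the Genotyping section, replace the carrier v non-carrier comparison with a treatment-by-e4-carrier interaction. Add that term to the linear regression of MRI change already stated under Data analyses, with its existing covariates.

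For each of NAA/Cr, Glx/Cr, GABA/Cr and CBF, report the KGT-placebo difference in carriers, the same difference in non-carriers, and the interaction with its 95% CI, labelled exploratory. State the expected precision: at best about ±1.5 to 1.6 SD at 30 participants with 30-50% carriers, and wider if carriers fall unevenly between arms.

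Reword the Discussion sentence to say that the pilot can give only an imprecise, hypothesis-generating estimate of whether genotype modifies the KGT effect.

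The cost is one model term and a less favourable stated claim. Conduct and data collection do not change.
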